## **Disaster Recovery Plans**

Study data will be regularly entered in to DataFax database that is supported and maintained by the NIAID. As with ongoing IMEP study data will maintained by the DataFax support team at NIAID/NIH with rigorous the back-up systems. The system has the advantage of generating

automatically pdf copies of the forms that can be printed to replace the records in case of disaster.

## 5. Statistical Considerations and Data Analysis

### A. Sample Size and Power Calculation(s)

*Cross-sectional surveys.* Sample size for cross-sectional surveys will be based on the SMC coverage. Assuming 60% average coverage of SMC by the combination of nonoptimal methods (pools of two groups), 300 children/arm will be needed to detect 10% increase in average coverage for two pooled groups with at least 85% power correcting for multiple tests and using two Fisher's exact tests. To account for cluster sampling with a minimum 10 clusters per arm, interclass correlation of 0.01 (based on a previous trial showing vaccine coverage (Dicko et al BMC Pub Health 2011), and 5% missing data, 446 children will be surveyed per group (total of 1784 children).

*Passive surveillance.*

Assuming a clinical malaria attack rate of 0.3 per child per year in “3 rounds” arm, to detect an absolute difference in attack rate of the 0.075 episode/chil/ year (corresponding to 25% reduction) in the “4 rounds” arm, with a one sided p-value of 0.025 and power of 80%, using a quasi poisson model accounting for 20 equally sized clusters per arm with intraclass correlation of 0.01 and 5% missing data we will need 1386 per arm, or 2,772 subjects total.

*Immunological parameters.* We will base our sample size calculations for immunological endpoints on the humoral immune response to AMA1. We select this response because AMA1 is highly immunogenic from among malaria antigens. Also, the intervention in this trial is directed at reducing the blood stage burden of parasites during the malaria season, and the response to AMA1 reflects exposure to blood stage forms of the parasite. In earlier serology studies of young children participating in an AMA-1 vaccine trial in Bancoumana, Mali (Sagara et al, Vaccine, 2009), we observed the peak antibody titer against AMA1 to occur near the end of the malaria season (among children receiving control vaccine), with geometric mean antibody levels of 120 antibody units (95% CI, 70-205). Antibody levels just prior to the start of the malaria season (before vaccination) were 40 (25-75) antibody units. Based on these data, 467 subjects per

group will provide 80% power, to detect a 2 fold or greater reduction in peak AMA1 antibody levels among the children receiving SMC, accounting for cluster sampling in 10 equally sized clusters with 0.01 intraclass correlation as well as 10% missing data given that samples may be inadequate or spoil during routine collection and transport.

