Despite the huge benefit provided by SMC, one of the concerns is that SMC will impair the acquisition of protective immune responses, thereby increasing the risk of disease in later years. Studies conducted in Mali and other countries have compared the susceptibility to malaria among children who received the intervention over a single season and the control group during the following malaria transmission season and have found a small increase in clinical malaria among children who received the intervention [Dicko et al 2008, Dicko et al 2011, Konate et al, 20011, Wilson A et al 2011]. None of these efficacy studies have assessed the impact of SMC on immunity to malaria when given for more than one transmission season. Under conditions of long term intervention, we hypothesize that immunity to liver-stage malaria antigens (reflecting exposure to infected mosquito bites) will be similar among children receiving SMC to that of children who will not receive SMC, but immunity to blood stage antigens will be markedly decreased (reflecting protection from blood stage infection). In this proposal, children will receive intervention in a stepped wedge fashion and be followed for a period up to 3 years. We are currently studying the acquisition of immunity to malaria among children recruited at birth as part of an immuno-epidemiological (IMEP) cohort study in Ouelessebouyou, where we plan to enroll up to 2000 children who will be followed up for 5 years. We will leverage this cohort of children as a control group for the proposed intervention study. This will provide insights into the acquisition of malaria immunity and may indicate whether the cessation of longterm SMC will increase risk of subsequent malaria and warrant additional control measures.

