## 4. Study Design

### A. Detailed Description of Study Design

#### *Overall design*

The study will use a cluster randomized design over three years. Eight sub-districts will be randomly selected among the 13 sub-districts of Ouelessebouyou but excluding the sub district of the Ouelessebouyou where the IMEP cohort study is ongoing. These eight sub-districts will be randomized so that the intervention begins in four districts during the first year (Year 1), in two sub-districts in the second year (Year 2) and in two remaining sub-districts in third year (Year 3). The target population is children aged 3-59 months of age in the district of the Ouelessebouyou in Koulikoro region, in Mali.

In Year 1, the implementation of SMC will occur in four randomly selected sub-districts in Ouelessebouyou. Villages in these sub-districts will be randomized at 1:1 ratio to receive either a door-to door delivery (DDD) or fixed point distribution (FPD) of SMC. They will also be randomized to receive SMC as directly observed therapy (DOT) or non-directly observed therapy (NDOT). A census of the target population (children aged 3-59 months) will be carried out in all the selected villages prior to the intervention. During this census, blood samples will be collected in a randomly selected subset of study population to gather baseline data on cellular and humoral responses to malaria antigens, parasites prevalence and density on blood smears and frequency of the molecular markers of the resistance to SP and AQ at the start of the transmission season. The census list will be used to deliver the intervention and will be regularly updated. SMC will consist of the administration of full treatment course of sulfadoxine-pyrimethamine plus amodiaquine (SP+AQ) at monthly interval during the malaria transmission starting in August 2014. Children will be followed passively for the determination of the

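### The 80% power for the SMC versus no-SMC antibody comparison assumes 10 clusters, but SMC is assigned to 4, 2 and 2 sub-districts and the never-SMC control is one non-randomised sub-district

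*Protocol*

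**What the plan says.** Section 5.A (Sample Size and Power Calculation(s), immunological parameters) opens the claim with "Based on these data, 467 subjects per" and continues "group will provide 80% power, to detect a 2 fold or greater reduction in peak AMA1 antibody levels among the children receiving SMC". The allowance for clustering is "accounting for cluster sampling in 10 equally sized clusters with 0.01 intraclass correlation", "as well as 10% missing data". No SD, significance level or sidedness is given for this calculation. The only information on spread is a geometric mean of 120 units with a 95% CI of 70 to 205, from an earlier vaccine trial whose sample size is not stated.

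Section 4.A (Overall design) fixes who gets SMC and when: "These eight sub-districts will be randomized so that the intervention begins in four districts during the first year (Year 1"), followed by two sub-districts in Year 2 and the last two in Year 3. The eight are drawn "excluding the sub district of the Ouelessebouyou where the IMEP cohort study is ongoing". In Year 3 all eight receive SMC. Villages are randomised only to delivery mode (Year 1) and to three or four rounds (Year 2).

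The never-SMC group is introduced in the Rationale: "We will leverage this cohort of children as a control group for the proposed intervention study". The Overall design adds that the comparison with IMEP children will be a separate analysis that allows for differences between the cohorts. The French text repeats the same design and the same 467.

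**The concern.** The effect being powered is SMC against no SMC (specific objective 2). The 10 clusters cannot be the units to which SMC was assigned, because the trial has only eight sub-districts. They are presumably villages, as in the coverage calculation, which uses at least 10 clusters per arm. Villages within a sub-district share a start year, so they do not replicate the assignment of SMC.

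The never-SMC side is weaker still. It is a single sub-district, outside the randomisation, with children recruited at birth. More villages or children sampled there still represent one sub-district. Its between-sub-district variance cannot be estimated from its own data, and any standing difference in transmission, age structure or care would look like an effect of SMC.

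Two things are at stake: a power figure that promises more than the design can support for one of the protocol's specific objectives, and an overstated degree of certainty if the sub-district level is left out of the analysis.

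**Working it through.** **Inputs from section 5.A:** 467 per group, 80% power, 2-fold reduction (ln 2 = 0.693), 10 clusters, ICC 0.01, 10% missing. **Assumed:** two-sided 0.05; 10 clusters in each group; missing data handled as N × 0.9; the ICC at sub-district level, varied from 0.0025 to 0.02.

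**1. The protocol's own figure.**
- Analysable children: 467 × 0.9 = 420.3, or 42.03 per cluster.
- Design effect: 1 + 41.03 × 0.01 = 1.41. Effective n: 420.3 / 1.41 = 298 per group.
- SD implied by 80% power: 0.693 / (1.96 + 0.842) × √(298/2) = 3.02 ln units.
- The quoted CI gives an SE of (ln 205 − ln 70) / 3.92 = 0.274, so this SD corresponds to an earlier sample of (3.02/0.274)² ≈ 121.

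So 467 is coherent with 10 clusters in each group, but it cannot be derived from the stated inputs alone. If 10 is the total (five per group), the implied SD is 2.65.

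**2. Same children and SD, with the sub-district as the cluster.** For k₁ and k₂ sub-districts, each design effect is 1 + (420.3/k − 1) × ICC. The SE is 3.02 × √(1/n_eff1 + 1/n_eff2), and normal power is Φ(0.693/SE − 1.96). The t-based figure uses the noncentral t with k₁ + k₂ − 2 degrees of freedom.

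Example, four sub-districts versus IMEP at ICC 0.01: design effects 2.04 and 5.19; effective n 206 and 81; SE 0.396; 0.693/0.396 = 1.75; power Φ(−0.21) = 42%.

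| Sub-district ICC | 4 v IMEP: normal / t | 4 v 2: normal / t | 2 v 2: normal / t |
|---|---|---|---|
| 0.0025 | 73% / 43% | 81% / 57% | 77% / 33% |
| 0.005 | 59% / 33% | 70% / 47% | 64% / 27% |
| 0.01 | 42% / 24% | 55% / 36% | 47% / 20% |
| 0.02 | 27% / 16% | 37% / 24% | 31% / 14% |

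For comparison, 10 v 10 at ICC 0.01 gives 80% (normal) and 75% (t, 18 df). In the IMEP column all 3 degrees of freedom come from the SMC side, so the t figure also assumes that IMEP shares that variance.

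**3. Ceiling.** At ICC 0.01, unlimited children in 4 v IMEP give 0.693 / (3.02 × √(0.01 × (1/4 + 1))) = 2.05, hence power of at most 54%.

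**4. If the sub-district component is ignored (4 v 1).** In units of SD², the village-level variance is 2 × 1.41/420.3 = 0.00671. The true variance adds ICC × 1.25.
- Component 0.0025: 1.96 × √(0.00671/0.00984) = 1.62, so the nominal 5% error is about 11%.
- Component 0.01: 1.96 × √(0.00671/0.01921) = 1.16, so it is about 25%.

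**The case against.** Several points on the other side stand.

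- The protocol does not hide the nature of the IMEP comparison. It is called a separate analysis that allows for cohort differences, and immune responses are listed as secondary outcomes.
- The comparison of one, two and three seasons is already planned for Year 3. A reader might infer that the randomised information is left unused; the Overall design shows otherwise.
- A reader might infer that 467 is an arithmetic mistake. It is not: it is coherent with 10 clusters per group, and the fault lies in the choice of unit.
- A reader might infer that 80% power is certainly not reached. The documents give neither the SD nor a sub-district ICC. At ICC 0.0025 the normal figures for the randomised contrasts are 77% and 81%. The low t-based figures largely reflect the small number of units: even at ICC 0, 2 v 2 gives only 45%.
- A reader might infer that village-level standard errors will be used. The protocol fixes no standard-error method for antibody titres, so the 11% to 25% is what would follow if they were.
- Immune endpoints are to be analysed by the exact number of treatments received, which brings in individual variation. That does not alter the fact that the start year, and so the number of seasons on offer, is set by sub-district.

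None of this supplies the replication that the power sentence assumes. Allowing for cohort differences adjusts for measured factors; it cannot stand in for a second never-SMC sub-district.

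**Conclusion.** The point holds as a fault in the power statement. The structural part needs no assumption: SMC is assigned to 4, 2 and 2 sub-districts, no randomised area is untreated at the Year 3 peak, and the never-SMC group is one non-randomised sub-district. The 10-cluster allowance therefore does not describe the comparison it is attached to, and the IMEP contrast confounds SMC with place.

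The size is conditional on a back-solved SD of about 3.0 ln units, two-sided 0.05 and an assumed sub-district ICC of 0.0025 to 0.02. On that basis every figure for four sub-districts versus IMEP is below 80%. The randomised contrasts reach about 80% only at the lowest ICC and by the normal approximation. The point deserves correction because the comparison carries specific objective 2, but it does not touch the trial's two primary outcomes.

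**What to change.** 1. Restate the immune power with the sub-district as the unit of SMC assignment, as a range over the assumed ICC, and state the SD, alpha, sidedness and whether 10 clusters is per group or in total.
2. Label the IMEP comparison as observational and not protected by randomisation, building on the existing description of it as a separate analysis.
3. Base randomised inference about seasons of SMC on the planned comparison of the 4/2/2 start-year groups, using sub-district summaries or a permutation test. Across all eight sub-districts there are 8!/(4!2!2!) = 420 allocations, so the smallest one-sided p is 1/420 = 0.0024. Pairwise tests are much coarser: 15 allocations for 4 v 2 (smallest p 0.067) and 6 for 2 v 2 (0.17), so a trend across all three groups is the workable form.
4. Optionally, add the Year 3 pre-season survey, when the start-year groups have had two, one and no seasons, as a supporting randomised analysis. Making it the main contrast would be a debatable trade, because it is not the end-of-season peak for which the study was sized. The number of children per start-year group in that survey is also not stated.

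Items 1 to 3 are changes of wording and analysis. The cost is a less favourable stated power.

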### **B. Planned Interim Analyses (if applicable)**

At the end of the first transmission season, data will be analyzed to determine the optimal mode of delivery by comparing primarily the coverage of SMC and secondarily the incidence rate of the clinical malaria between the four intervention arms. In addition, descriptive analysis of the baseline frequencies of the immunological parameters, and molecular markers of the resistance of *P. falciparum* to SP and AQ, will also be performed at the end of Year 1.

Data collected in Year 2 will be used to determine the optimal frequency of the SMC rounds by comparing primarily the incidence of clinical malaria and secondarily the parasite prevalence at the end of season between the 2 arms. Descriptive analysis of immunological parameters and markers of drug resistance will also be performed.

Details of the statistical methods are provided below in the final analysis plan.

### **C. Final Analysis Plan**

*Describe statistical methods that will be used to analyze data.*

Data will be entered and verified using DataFax. The cleaned database will be exported to Stata (Houston Texas USA) or SAS for analysis. An intention-to-treat analysis will be used except for the immunological endpoints for which the exact number of the SMC treatments received will be considered.

SMC coverage will be determined using the information on the SMC card and from interview of parent or care giver and will be determined as the proportion of children who received all the treatments at all the SMC rounds during the transmission season. The proportion of children who received at least the first treatment dose of the SMC will be also estimated as secondary endpoints for SMC coverage. SMC coverage will be compared between arms and years of

interventions with 95% confidence intervals adjusted for cluster design (using cluster option in Stata for example). The DDD+NDOT arm will be considered as control group.

The census of the children will be updated at each round and at the end of the transmission season to allow a good estimation of person-time of follow-up. Cases of the clinical malaria will be recorded and the incidence rate of the clinical malaria defined as the number of clinical malaria episodes divided by total child days at risk. Children will not be considered at risk 21 days after a clinical malaria episode. Incidence rates of clinical malaria will be compared between treatment arms using generalized estimating equation to estimate the incidence rate ratio, with adjustment for age, previous SMC regimens and the lack of independence among repeated episodes in the same child.

Proportions of other secondary endpoints such as parasite prevalence, prevalence of anemia and frequency of molecular markers of resistance to SP and AQ and adverse events associated with study drugs will be estimated and compared between groups using generalized linear models with 95% confidence intervals, adjusted for cluster design and potential confounding variables such as age and use of ITN.

Differences at baseline will be compared using Chi-squared or Fisher's exact tests as appropriate for categorical variables and by analysis of the variances for quantitative variables that are normally distributed. Nonparametric tests will be used for non-normally distributed data.

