In Year 3, all study children in the eight selected sub-districts will receive SMC by optimal method and frequency determined in Year 1 and Year 2 and will be followed passively for clinical malaria episodes through the end of the season. Venous blood samples will be collected at the beginning (July/August) and the end of the transmission season (November/ December) in a subset of randomly selected children to assess humoral and cellular responses to malaria

antigens as well as the prevalence of malaria parasitemia among children who received SMC during one, two and three malaria transmission seasons. These outcomes will also be compared to those among children in the IMEP cohort who never received SMC, in a separate analysis taking into account the differences and similarities between the cohorts.

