#### ***Census and randomization***

Once community consent to the trial is obtained, a household census will be conducted and all households within the study areas with children under 5 years of age will be identified. At the time of census, a preliminary screening of potentially eligible children will be undertaken. Eligible children will be identified and written informed consent will be obtained from their caretakers for their inclusion in the trial. Children entered into the trial will be assigned a unique ID number and their demographic data (date of birth and/or age, and gender) will be collected.

The census will be updated at each SMC round and potentially eligible participants (such as children who did not reach the age of three months during the previous round) will be identified and screened for eligibility and enter into the study. This updated census will collect information on migration and death of children enrolled into the study for precise estimation of person-time of follow-up.

The unit of randomization will be village and all eligible children in a village will be allocated to the same study arm (DDD+ DOT or DDD+NDOT or FPD+ DOT or FPD + NDOT) to avoid confusion in Year 1. Villages in the selected sub-districts will be randomized at 1:1 ratio to receive either a door –to-door delivery (DDD) or fixed point distribution (FPD) of SMC. They will also be randomized to receive SMC as directly observed therapy (DOT) or a non-directly observed therapy (NDOT). In Year 2, villages in the two newly randomly selected districts will be randomized into two groups to receive either three or four rounds of SMC.

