### ***Inclusion and exclusion criteria***

Children of either sex aged 3-59 months of age at the start of each period of drug administration will be eligible for inclusion in the trial, provided that parental consent is obtained. Children under the age of three months on the date of the start of drug administration will be excluded that year, as SMC is not recommended for children in this age group whose risk of acquiring malaria is low. Children who reach the age of 59 months or more at the end of the first or second years of treatment will not receive SMC in subsequent years. Exclusion criteria will be as limited as possible to make the results of the trial broadly applicable and will include i) a severe, chronic illness, ii) a known allergy to one of the study drugs, iii) known HIV positive subjects using Cotrimoxazole. [Children with acute clinical malaria at the time of SMC drug administration will be treated by ACT and will not be given SMC drugs during that round as per WHO recommendation. They will receive SMC drugs during subsequent cycles.](#)

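### The immunity endpoints are analysed by SMC treatments received, a count that depends on malaria and on age, instead of by the randomised start year

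*Protocol*

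**What the plan says.** Protocol section C, Final Analysis Plan, adopts intention-to-treat "except for the immunological endpoints for which the exact number of the SMC treatments received will be considered". The French version (section 5.3) says the same. Other sections settle what that number measures:

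- Inclusion and exclusion criteria: "Children with acute clinical malaria at the time of SMC drug administration will be treated by ACT and will not be given SMC drugs" in that round. They rejoin at later rounds.
- Same section: "Children under the age of three months on the date of the start of drug administration will be excluded that year". Census and randomization nevertheless admits at a later round newly eligible children, "such as children who did not reach the age of three months during the previous round". On either reading the youngest children accumulate fewer treatments. At the upper end, children who reach 59 months by the end of Year 1 or Year 2 "will not receive SMC in subsequent years".
- Overall design: eight sub-districts are randomised to begin SMC in Year 1 (four), Year 2 (two) or Year 3 (two). In Year 3 immune responses are compared "among children who received SMC during one, two and three malaria transmission seasons" and, separately, with the IMEP cohort that never received SMC.

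The Final Analysis Plan names age as a covariate for malaria incidence and for the secondary endpoints expressed as proportions. It names no covariate for the immune endpoints.

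**The concern.** Objective 2 is about immunity, and the Rationale expects blood-stage responses to be lower under SMC. The number of treatments received is tied to those responses in two ways that have nothing to do with an effect of SMC.

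**Malaria route.** A more exposed child is more often ill on a distribution day, loses more rounds, and has more blood-stage antibody because of the infections. Low counts then go with high antibody, which looks like the hypothesised effect.

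**Age route.** A child with three seasons is at least about 3 + 24 = 27 months old in Year 3, whereas the one-season group includes infants of 3 months. If antibody rises with age, high counts go with high antibody, which is the opposite direction.

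A real loss of immunity could be masked, or a false one reported. The design already contains a randomised contrast, the start year, that neither route affects, and the stated analysis sets it aside.

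**Working it through.** **1. The plan's own AMA1 figure (context, not disputed).** 467 × 0.90 = 420 evaluable per group. With 10 clusters of 42, the design effect is 1 + 41 × 0.01 = 1.41, so the effective n is 420/1.41 = 298. At 80% power, two-sided 0.05 (assumed, since the protocol gives no alpha here) and a difference of ln 2, the required SD on the ln scale is √[298 × (ln 2)² / (2 × (1.96 + 0.84)²)] ≈ 3.02. The quoted interval of 70–205 gives an SE of ln(205/70)/3.92 = 0.274, so 467 is consistent with about (3.02/0.274)² ≈ 121 children behind that interval. The protocol does not report that number, so 467 cannot be confirmed. The result is used only to set the upper residual SD below.

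**2. Chance of being ill at a round.** Assume a one-week illness window and all episodes within a 26-week season.

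- At the 0.3 episodes per child-year assumed for the three-round arm in the sample size section: 0.3/26 ≈ 1.2%.
- At the roughly 2 per child-year quoted for the area in 2008 (French section 4.1): 2/26 ≈ 8%.

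**3. Simulation with no SMC effect on antibody.** 420 children in each of the one-, two- and three-season start groups; three rounds per season; eligibility from 3 months; a sick child loses the round; 600 runs per scenario. Assumed, because the protocol gives no values: 85% coverage per round, a slope of 0.5 of ln antibody on ln exposure, an age slope of 0, 0.25 or 0.5 ln units per year, and residual SD 1.5 or 3.0.

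| Scenario | Analysis | Apparent GM ratio, 9 v 0 treatments | False-positive rate |
|---|---|---|---|
| Malaria route, 1.2% per round | count | 0.95–0.96 | about 5–6% |
| Malaria route, 8% per round | count | 0.72–0.73 | 13–39% |
| Malaria route, 8% per round | count, age-adjusted | 0.68–0.69 | 13–42% |
| Malaria route, 8% per round | count, adjusted for age and start group | 0.48 | 26–73% |
| Age route, 0.25 per year | count | 1.7 | 32–84% |
| Age route, 0.5 per year | count | 3.0 | 82–100% |
| Both routes, 8% and 0.25 per year | count | 1.23–1.25 | 9–19% |

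Age adjustment removes the age route but not the malaria route. Adding start group to the count model enlarges the malaria route, because the comparison then rests on who missed rounds within a group.

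For full receipt of three seasons against one (9 v 3 treatments) the ratios are closer to 1. The malaria route at 8% has a slope of about −0.036 per treatment, so exp(6 × −0.036) = 0.81. The age route becomes 1.7^(6/9) = 1.4 to 3.0^(6/9) = 2.1.

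**4. By randomised start group, same data.** The GM ratio for three seasons against one is 0.98–1.01 in every scenario, with a false-positive rate of about 3–7%. These runs ignore clustering, so real precision would be lower.

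**The case against.** The protocol says only that the number of treatments will be considered. It fixes no regression and does not rule out age adjustment, which an SAP not shown here could supply. That largely answers the age route. It does not answer the malaria route, and the sentence still removes these endpoints from intention-to-treat.

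At the protocol's own 0.3 episodes per child-year the malaria route is negligible. This stands. That rate, however, is an assumption for children receiving three rounds of SMC, and the first round each season comes before that season's protection. The area figure of 2 per child-year is not stated to have been measured under SMC, so the two rates are best read as ends of a range.

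A reader might infer a false two-fold fall in AMA1, the very size the study is powered to detect. Suppose 2% of rounds are skipped for malaria, 8% are missed otherwise, and antibody is three-fold higher after malaria. Within one season the slope is −ln 3 × 0.02/0.10 = −0.220 per round, and exp(3 × −0.220) = 0.52. The documents do not support that reading:

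- The skip rates are not in them.
- The rise from 40 to 120 is a seasonal change in a group geometric mean, not the effect of an episode.
- The figure compares three rounds with none, although only 0.10³ = 0.1% of children would have none.
- In the Year 3 comparison most of the variation in count comes from start year. With equal malaria in all groups, the variance within groups is 6 × 0.10 × 0.90 = 0.54 and between groups 0.90² × 6 = 4.86. The slope is −ln 3 × (6 × 0.02 × 0.90)/5.40 = −0.022, and exp(6 × −0.022) = 0.88, or about 0.9 for 9 v 3 rounds.

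Finally, analysis by start year cannot repair the comparison with the never-SMC IMEP cohort. This also stands.

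**Conclusion.** The point holds as a flaw in the basis of analysis, not as a prediction of a particular false result. For the immune endpoints alone, the plan replaces a randomised contrast with a count that depends on malaria and age. The malaria route runs from negligible (0.3 episodes per child-year) to a geometric mean ratio of about 0.7 for 9 v 0 treatments (2 per child-year). The age route is large if age is left out. They act in opposite directions, so the net sign is open. These sizes rest on the assumed illness window, coverage, antibody slopes and variation in exposure.

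It should be corrected, but it does not threaten the trial's main decisions. Immune responses are secondary trial outcomes, although long-term immunity is part of the overall objective. The coverage and malaria-incidence primaries remain intention-to-treat.

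**What to change.** 1. Make the main within-trial immunity comparison by allocated start year (Year 1, 2 or 3 sub-districts), adjusted for age and clustering.
2. Include a comparison in children about 27–59 months old in Year 3, who were age-eligible in all three seasons, and ensure that the immunology sample contains enough of them in every start group. The sampling should be settled before the surveys.
3. Keep treatments received as a supportive, age-adjusted analysis, with a sensitivity analysis that counts rounds skipped for malaria as allocated.

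The treatment rules are untouched. The cost is a change of analysis wording and attention to age in the sampling. Three limits should be stated: start year is randomised over only eight sub-districts (4/2/2), so precision is limited; the age-restricted result does not cover children under 27 months; and the IMEP comparison remains non-randomised.

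### The cluster-robust method suggested for Year 1 coverage has a type I error of roughly 6–8% instead of 5% at 10 equal villages per arm, unless a small-sample correction is added

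*Protocol*

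**What the plan says.** The protocol's Census and randomization section fixes the cluster: "The unit of randomization will be village and all eligible children in a village will be allocated to the same study arm".

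Section 5.A sizes the cross-sectional survey "with a minimum 10 clusters per arm" and an intraclass correlation (ICC) of 0.01. The comparison it powers is a pooled one: "300 children/arm will be needed to detect 10% increase in average coverage for two pooled groups with at least 85% power".

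Section 5.C says that coverage will be compared between arms and between years, with 95% intervals that allow for the clustering, "using cluster option in Stata for example". It then adds: "The DDD+NDOT arm will be considered as control group". It gives no small-sample correction and no reference distribution, and it excludes neither.

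Section 4.A attaches a decision to the result. If the arms differ significantly in neither coverage nor malaria incidence, the easiest delivery method is recommended for Year 2.

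**The concern.** Naming a control arm implies comparisons of one arm with another. Such a comparison draws its variance only from the villages in those two arms. At the planning minimum that is 10 against 10, however many villages the trial has in total.

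Two things then go wrong with an ordinary robust variance. It is built from residuals around the fitted arm means, so on average it is too small. It is also referred to a normal distribution, or to a t distribution with more degrees of freedom than the 18 that 20 villages in two arms provide. Both make the intervals too narrow.

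At stake is the selection rule. A false positive on coverage removes the default to the easiest method. The mode chosen is then carried into Year 2 and, in Year 3, into all eight sub-districts.

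**Working it through.** **Inputs from the protocol.** 300 children per arm before inflation, at least 10 villages per arm, ICC 0.01, 5% missing, reference coverage 60% (all Section 5.A); 95% intervals, hence a nominal 5% two-sided level (Section 5.C).

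**Assumptions.** The spread of village sizes in the survey is not stated, so a range is used. An ICC of 0.05 is tried beside 0.01. How the software option behaves is not in the documents, so several versions are shown: no finite-sample factor, or a factor G/(G−1), where G is the number of villages in the model; and a normal or a t(G−1) reference.

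**The plan's own figure.** Inflating 300 for 10 clusters gives 300 × 0.99 / (1 − 300 × 0.01/10) = 297/0.7 = 424.3. Dividing by 0.95 gives 446.6, against the stated 446. The sample size reproduces. It implies about 424/10 ≈ 42 children analysed per village.

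**Closed form, 10 v 10 equal villages.** The expected robust variance is (10 − 1)/10 = 0.9 of the true variance. With a factor it is v = 0.9 × G/(G−1). If c is the critical value used, the true error is P(|t₁₈| > c√v).

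| Factor and reference | c | v | c√v | Type I error |
|---|---|---|---|---|
| none, normal | 1.960 | 0.900 | 1.859 | 7.9% |
| 20/19 (two-arm model), normal | 1.960 | 0.947 | 1.908 | 7.3% |
| 20/19, t₁₉ | 2.093 | 0.947 | 2.037 | 5.7% |
| 40/39 (four-arm model), normal | 1.960 | 0.923 | 1.883 | 7.6% |
| 40/39, t₃₉ | 2.023 | 0.923 | 1.943 | 6.8% |

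**Unequal villages.** Beta-binomial simulation with no true difference, 60% coverage, about 42 children per village, 10 villages per arm, ICC 0.01–0.05, finite-sample factor applied:

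| Size CV (assumed) | Normal reference | t reference |
|---|---|---|
| 0.4 | 7.6–8.2% | 6.1–7.5% |
| 0.5 | 7.8–9.0% | not tabulated; between the rows above and below |
| 0.7 | 9.1–10.0% | 7.5–9.2% |

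**More villages.** With equal sizes and a normal reference, 15 villages per arm give 6.3–6.8% and 20 per arm give 5.7–6.0%. For the pooled contrast, 20 v 20 at the minimum, v = 0.95 × 40/39 = 0.974. On 38 degrees of freedom the error is 6.1% with a normal reference and 5.3% with t₃₉; with no factor it is 6.4%.

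**Corrected methods, 10 per arm.** An unweighted t-test on village proportions with 18 degrees of freedom gives 4.7–5.2% for CV 0 to 0.7. A robust variance with K/(K−1) per arm (K villages in the arm) and t₁₈ gives 4.9–5.1% at equal sizes, but 5.5–5.8% at CV 0.4 and 6.6–7.0% at CV 0.7. A Kauermann–Carroll variance with t₁₈ gives 4.8–5.8% for CV 0 to 0.5.

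**The case against.** The strongest reply is that the protocol does not commit to the criticised method. The Stata option is an example, SAS is also allowed, and the French text (section 5.3, Plan d'analyse final) makes the same commitment to cluster-adjusted intervals without naming any option. A correction is not excluded, and an analysis plan that is not shown may specify one. This stands as a limit: a reader might infer that an uncorrected analysis is fixed, and it is not. It does not remove the point. Section 5.B sends the reader to 5.C for the statistical methods, and the one method named there for this primary outcome is one that needs correcting.

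Ten villages is also a minimum. Section 5.A assumes 20 clusters in each of two arms for Year 2, all within two sub-districts. That is 40/2 = 20 villages per sub-district, and at the same density four sub-districts and four arms would give about 20 per arm in Year 1. This is an inference, and the survey could use fewer villages, but at 20 equal villages per arm the excess is small. It is small too in the pooled contrasts on which power was based.

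Two stronger readings are tempting. One is that the error is 8–9% outright. That needs unequal villages, and the protocol gives no spread; with equal villages its own inputs give roughly 6–8%. The other is that the inflation is proportionally worse at a multiplicity-corrected level. Section 5.A mentions correction for two tests but states no alpha, and no corrected level is given for the arm-versus-control comparisons, so no figure can be attached.

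**Conclusion.** The point holds as an inexpensive improvement to the analysis plan. It does not show the design or the sample size to be faulty.

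Used without a small-sample correction at 10 equal villages per arm, the suggested method has a type I error of 5.7–7.6% with the finite-sample factor and 7.9% without it. With the factor that is about 1.1 to 1.5 times the nominal 5% (5.7/5 and 7.6/5). At an assumed size CV of 0.5 and a normal reference it is about 8–9%. At 20 equal villages per arm, or in the pooled contrasts, it is about 5–6%.

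The direction is the same in every scenario computed; the size depends on the number of villages surveyed, their spread and the reference distribution. Malaria incidence also supports the choice of delivery mode, which tempers the consequence of a false positive on coverage.

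**What to change.** In Section 5.C, replace the Stata example with a named small-sample method for comparing coverage between arms. Either of these would do:

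- a t-test on village-level coverage proportions; or
- a cluster-robust variance with a small-sample correction (Kauermann–Carroll or Mancl–DeRouen), with t quantiles on (villages compared − 2) degrees of freedom.

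The t-test held its level best when village sizes varied. It weights villages rather than children equally, so the text should say which average is meant. A simple K/(K−1) factor with t₁₈ is not enough if sizes vary widely.

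The cost is one sentence and wider intervals. With 10 equal villages per arm, the correct multiplier of the true standard error is t₁₈ = 2.101, against c√v of 2.037 to 1.883 in the rows with the finite-sample factor. The intervals widen by about 3% (2.101/2.037) to 12% (2.101/1.883). No change to the design or to the 446 children per group is needed.
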